### Statistical analysis

After completion of the study, all eligible carriers who have been randomised to the treatment arm and received at least 1 dose of eplerenone will be used in the analyses of the primary and secondary efficacy endpoints, as well as in the safety analysis. Safety will be assessed by summarising the incidence and type of adverse events and the changes in laboratory parameters. The proportion of carriers experiencing serious adverse events and the proportion of carriers with noteworthy changes in laboratory parameters will be compared between treatment groups. The analysis of primary endpoints and secondary endpoints will be performed according to their assigned treatment group in accordance with the intention-to-treat principle. Additional analysis sets may be used in exploratory analyses. The number of subjects withdrawing from the study will be tabulated by their reasons for withdrawal and by treatment group. Potenzial biases due to withdrawal of subjects will be investigated. Baseline characteristics will be compared using chi-squared test (or Fisher’s exact test if appropriate). If differences are found, caution will be exercised when interpreting the results of the analyses between groups and methods may be modified to adjust for this difference.

The primary outcome will be presented by Kaplan-Meier curves for the treatment group, followed by the stratified log-rank test using stratification variables. Multivariate analysis will also be used to compare the endpoints between the two groups, adjusting for other variables including sex, age and screening centre. For missing data, the last observations made will be used. Unless stated otherwise, all secondary analyses will be performed using the same subjects included in the primary analysis. Secondary variables will be analysed using an appropriate statistical test, depending on the nature of the variable. Changes in parameters over time in the different treatment groups will be analysed using repeated measurement analysis or techniques that evaluate the timing of endpoints, when appropriate. For all tests, a *p*-value < 0.05 is considered statistically significant. Statistical analysis will be performed in SPSS (IBM SPSS Inc., Chicago, IL, USA; newest version at moment of analysis).

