## Baseline results

In May 2014, the first participant was included into the study. Because of slow recruitment, in January 2018 it was decided to stop further inclusion of participants and complete the protocolled follow-up duration with the included cohort (*N* = 84). At this point, it had become clear that it was not realistic to assume that enough participants would be included to reach the originally defined composite primary endpoint (Tab. 3). Instead of a composite dichotomous endpoint, i.e. using the pre-specified cut-off values, individual components of the primary endpoint will now be analysed on a continuous scale to investigate possible significant differences. The statistical analysis plan was amended accordingly, and the decision to amend the study design, i.e. to stop inclusion of participants and to continue with the included cohort, was supported by the DSMB and the medical ethics committee. The primary objective remains showing that eplerenone retards disease progression. The majority of participants have now finished the study and the remaining participants are expected to finish in 2021.

An overview of the baseline characteristics of the 84 participants is provided in Tab. 4. By design, at baseline, all participants were in NHYA class I and had an LVEF > 45% and less than 2500 ventricular premature complexes (VPCs) during 24-hour Holter monitoring. Mean LVEF was 60% (±0.04). The median number of VPCs was 8 (0-1861). Baseline CMR scans were obtained for all 84 participants, but image quality was insufficient to perform adequate analyses in six cases. In the remaining 78 cases, as many as 14 cases (18%) showed LGE, mainly in the inferolateral left ventricular wall, suggestive of myocardial fibrosis. The six cases with insufficient image quality will be included for analysis of the other endpoints. An illustrative example is shown in Fig. 2. There were no statistically significant differences between the two groups in any of the baseline characteristics.

**Table 4 Tab4:** Baseline characteristics: no statistical differences between eplerenone and control group

	All	Eplerenone group	Control group
Number, *n*	84	42	42
Age at inclusion, years (SD)	39.5 (±13.1)	40.2 (±13.0)	38.8 (±13.4)
Male sex, *n* (%)	37 (44)	18 (43)	19 (45)
Body mass index, kg/m^2^ (SD)	25.7 (±4.8)	26.5 (±5.6)	24.9 (±3.6)
Systolic blood pressure, mm Hg (SD)	124 (±16)	128 (±17)	121 (±13)
Diastolic blood pressure, mm Hg (SD)	74 (±11)	75 (±10)	74 (±11)

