ECG repolarisation abnormalities, *n* (%)	18 (21)	13 (31)	5 (12)
VPC, *n* (range)	8 (0–1861)	8 (0–1498)	12 (0–1861)
LVEDV, ml (SD)	157 (±28)	160 (±23)	154 (±34)
LVEF, % (SD)	60 (±0.04)	60 (±0.04)	59 (±0.05)
LV-LGE, *n* (%)	14 (18)	9 (22)	5 (13)
RVEDV, ml (SD)	178 (±34)	179 (±27)	176 (±42)
RVEF, % (SD)	52 (±0.04)	52 (±0.04)	51 (±0.04)

*SD* standard deviation*, ECG* electrocardiogram, *VPC* ventricular premature complexes, *LVEDV* left ventricular end-diastolic volume, *LVEF* left ventricular ejection fraction, *LV-LGE* left ventricular late gadolinium enhancement, *RVEDV* right ventricular end-diastolic volume, *RVEF* right ventricular ejection fraction

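### The statement that no baseline characteristic differs significantly fails against Table 4 under the plan's own test, and it feeds a rule that lets baseline comparisons decide whether methods change

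*Protocol article*

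**What the plan says.** The claim appears three times in the protocol article. The Baseline results section states "There were no statistically significant differences between the two groups in any of the baseline characteristics", the Abstract has the same sentence, and Table 4 is titled "Baseline characteristics: no statistical differences between eplerenone and control group".

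The Statistical analysis section supplies the means to check it:

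- The test: "Baseline characteristics will be compared using chi-squared test (or Fisher’s exact test if appropriate"). No test is named for continuous baseline variables.
- The threshold: "For all tests, a *p*-value < 0.05 is considered statistically significant". Sidedness is not stated; two-sided is assumed below.
- The consequence: if differences are found, results are to be interpreted with caution and "methods may be modified to adjust for this difference". How they would be modified is not said.
- Separately, and whatever the baseline tests show, a multivariate analysis is planned, "adjusting for other variables including sex, age and screening centre".

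Table 4 gives "ECG repolarisation abnormalities" in 13 (31%) of the eplerenone group and 5 (12%) of the control group. Systolic pressure is 128 (±17) and 121 (±13) mm Hg. Each group has 42 participants.

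**The concern.** A difference of 31% against 12% with 42 per arm is large enough that a claim of no significant difference calls for a check. The claim covers every characteristic, so one counterexample makes it wrong.

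The statement also does work inside the plan, because caution and a possible change of methods depend on whether differences are found. The rule itself is weak: in a randomised trial any baseline difference is due to chance, and a baseline test says nothing about whether a variable predicts the outcome. Choosing the model this way leaves it open until data have been seen. That matters more here than usual. The trial is open-label, most participants had finished at the time of writing, and the primary analysis has moved from a dichotomous composite to individual components on a continuous scale.

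**Working it through.** **Denominators for the repolarisation row.** 13/42 = 31.0%, 5/42 = 11.9% and 18/84 = 21.4% reproduce the printed 31, 12 and 21. Smaller denominators do not: 13/41 = 31.7% would print as 32, and 18/83 = 21.7% as 22. The counts can therefore be taken as 13/42 and 5/42.

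**Chi-squared, the plan's default.** For a 2×2 table with cells a = 13, b = 29, c = 5, d = 37:

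χ² = N(ad − bc)² / (product of the four margins) = 84 × (481 − 145)² / (42 × 42 × 18 × 66) = 9,483,264 / 2,095,632 = 4.53, so p = 0.033 on 1 degree of freedom.

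The smallest expected count is 42 × 18 / 84 = 9, so small counts give no reason to move to Fisher's test.

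| Test, repolarisation row | p |
|---|---|
| Pearson chi-squared | 0.033 |
| Barnard | 0.035 |
| Boschloo | 0.035 |
| Fisher's exact | 0.061 |
| Chi-squared with Yates correction | 0.063 |

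**Systolic pressure.** A t-test from the printed summaries:

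SE = √((17² + 13²)/42) = √(458/42) = 3.30; t = (128 − 121)/3.30 = 2.12; p = 0.037 (the same for Welch).

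The means and SDs are printed as whole numbers. Over all values that round to them, p runs from 0.014 to 0.082. About 81% of the grid of such values lies below 0.05; this is a share of the grid, not a probability.

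**The other rows agree with the statement.** Age 0.63, sex 0.83, BMI 0.12, diastolic pressure 0.66, LVEDV 0.36, LVEF 0.33, LV-LGE 0.33, RVEDV 0.71, RVEF 0.27. The CMR rows assume that the 78 readable scans split 41 and 37, which is not printed; a 40/38 split gives 0.28 for LV-LGE. The ejection fraction SDs, printed as 0.04 and 0.05, are read as 4 and 5 percentage points. The ventricular premature complex row cannot be tested from a median and range.

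**What chance alone would give.** Table 4 has 12 characteristics. If they were independent and each tested at 0.05, the chance of at least one below 0.05 is 1 − 0.95¹² = 0.46. The chance of two or more is 1 − 0.540 − 0.341 = 0.12.

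**The case against.** The strongest defence is that the authors may have used Fisher's test or a continuity correction for repolarisation (p about 0.06), and a rank test for systolic pressure or unrounded values that fall above 0.05. The statement would then be true. This cannot be excluded, but both conditions must hold together, and the first departs from the plan's stated default without a small-count reason. For systolic pressure the defence stands in part: no test is named for continuous variables and the rounding range crosses 0.05, so that row is probable rather than established.

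A reader might infer more than this, and the documents do not support it:

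- *That the wrong statement switches adjustment off, or that needed adjustment will be skipped.* The rule refers to differences, not to significant ones, and only permits a change. The multivariate analysis is planned regardless, and its covariate list is open. A baseline p-value does not establish need.
- *That randomisation failed.* One or two nominal differences among 12 are unremarkable.
- *That the imbalance tilts the comparison against eplerenone.* More repolarisation abnormalities, more LGE (9 against 5) and a larger LVEDV (160 against 154 ml) point one way. LVEF (60 against 59%), RVEF (52 against 51%) and median ventricular premature complexes (8 against 12) point the other. The effect would also depend on whether change or final values are analysed.
- *That adjustment is worth a known number of participants.* The variance of ANCOVA relative to change scores is (1 + r)/2. At assumed correlations of 0.5 to 0.8 that is 0.75 to 0.90, equivalent to 84/0.75 − 84 = 28 down to 84/0.90 − 84 = 9 extra participants. The article gives no correlation and does not commit to change scores, so this is no part of the point.

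Finally, the article says the statistical analysis plan was amended for the continuous analysis. That plan is not shown and may already fix the model. The article's silence on baseline values as covariates is therefore not counted as an error.

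**Conclusion.** The statement in the Abstract, the Baseline results section and the Table 4 title is contradicted by Table 4 under the plan's own default test and threshold. The contradiction is firm for ECG repolarisation abnormalities (chi-squared 4.53, p = 0.033, from counts not subject to rounding) and probable for systolic pressure (p = 0.037; 0.014 to 0.082 over rounding). It assumes two-sided testing and, for systolic pressure, a t-test.

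The differences are nominal and compatible with chance. No planned analysis, sample size or endpoint is shown to change because of them. The methodological weakness is the stated rule, which lets baseline comparisons decide whether methods change and which the incorrect statement feeds. It is worth correcting because the remedy is cheap.

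**What to change.** 1. Correct the three statements to report the repolarisation difference and, if the unrounded data confirm it, the systolic pressure difference. Alternatively, state which test was used for each row and print the p-values.
2. Delete the rule that ties a change of methods to baseline comparisons. Replace it with covariates fixed on prognostic grounds before outcomes are compared by arm: for each continuous component its own baseline value, plus centre (the randomisation stratum), age and sex. If the amended analysis plan already does this, the article need only say so.
3. If wanted, add adjustment for baseline repolarisation abnormality as a sensitivity analysis, labelled as chosen after seeing the baseline data. Promoting it to the main model because of its p-value would repeat the practice being removed.

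The cost is a text correction and about one sentence in the analysis plan. All these covariates are part of the baseline assessment, although an analysable CMR baseline exists for only 78 of the 84. With four centres the model spends 3 degrees of freedom on centre and one each on age, sex and the baseline value, 6 in all.

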**Fig. 2 Fig2:**
[figure not shown]
Left ventricular delayed contrast enhancement in PLN p.Arg14del carrier. Example of left lateral delayed contrast enhancement (*arrow*; short axis CMR image) in the left ventricle of PLN p.Arg14del carrier. *CMR* cardiac magnetic resonance, *PLN* phospholamban

## Discussion

The PLN p.Arg14del founder mutation causes DCM and ACM and is associated with an increased risk of malignant ventricular arrhythmia and heart failure [1, 8, 9]. Although DCM and ACM are considered separate entities by both the American Heart Association [22] and the European Society of Cardiology [23], they do have overlapping clinical features [24–26]. This is particularly true in PLN p.Arg14del cardiomyopathy, where we find significant clinical overlap [1].

The multicentre prospective randomised clinical iPHORECAST study aims to show that preventive treatment (eplerenone) can prevent or delay disease onset in presymptomatic PLN p.Arg14del carriers. Given eplerenone’s potent antifibrotic effects, we anticipate it may retard disease progression. Eplerenone has been shown to be well tolerated with minimal side-effects, even in advanced heart failure patients. The most significant side-effect is hyperkalaemia, which mainly occurs in combination with other potassium-sparing drugs and/or renal impairment. The presymptomatic subjects in the present study, who all have normal kidney function are at very low risk for these side-effects. By using strict inclusion and exclusion criteria and follow-up monitoring, we are convinced that the use of eplerenone in the present study is safe.

The primary objective of this study is to assess the effect of eplerenone on disease onset and progression. To comply with daily clinical practice and demonstrate overall disease progression, a composite endpoint of CMR parameters (CMR volumes, systolic function and fibrosis), electrocardiographic parameters (QRS voltage, ventricular ectopy), signs and/or symptoms related to DCM and ACM, and cardiovascular death is adopted as the primary endpoint. Serum markers of fibrosis, apoptosis, haemodynamic status and inflammation are measured to investigate whether they can predict disease progression. Of note, as discussed in the baseline results, the actual number of participants was lower than projected. As a result, we will now perform an adapted assessment of the primary endpoint but are hopeful that meaningful results will be obtained. As to their clinical characteristics, the participants are a good reflection of clinical practice; indeed, many of these presymptomatic PLN p.Arg14del carriers already have subtle signs of disease, including repolarisation abnormalities of the ECG and frequent VPCs. Moreover, LGE on CMR, indicative of fibrosis, was observed in as many as 18% of the participants at the start of the study thereby supporting the rationale to study the effect of eplerenone.

In conclusion, iPHORECAST is a multicentre, randomised, controlled trial, designed to examine whether treatment with eplerenone in presymptomatic PLN p.Arg14del carriers can prevent or delay disease onset.

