**Methods:**

iPHORECAST has a multicentre, prospective, randomised, open-label, blinded endpoint (PROBE) design. Presymptomatic PLN p.Arg14del carriers are randomised to receive either 50 mg eplerenone once daily or no treatment. The primary endpoint of the study is a multiparametric assessment of disease progression including cardiac magnetic resonance parameters (left and right ventricular volumes, systolic function and fibrosis), electrocardiographic parameters (QRS voltage, ventricular ectopy), signs and/or symptoms related to DCM and ACM, and cardiovascular death. The follow-up duration is set at 3 years.

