### Study endpoints

The primary and secondary endpoints are listed in Tab. 3. The primary endpoint is a multiparametric assessment of disease progression defined as a responder-based composite primary endpoint (Tab. 3). If one of the predefined parameters of the composite primary endpoint is reached, CMR imaging is performed and study end date recorded. After a follow-up period of 3 years, outcomes will be assessed by an independent adjudication committee blinded to the allocated group. In case of a favourable trend (but no significant effect as yet), the DSMB may advise continuing the study for 2 more years (“adaptive design”).

**Table 3 Tab3:** Primary and secondary endpoints

*Primary endpoint*^a^
LV end-diastolic volume, increase > 10% (assessed with CMR)
LV ejection fraction, absolute decrease > 5% (assessed with CMR)
RV end-diastolic volume, increase > 10% (assessed with CMR)
RV ejection fraction, absolute decrease > 5% (assessed with CMR)
Late enhancement, absolute increase > 5% (assessed with CMR)
QRS voltage, decrease > 25% (ECG, measured in I, II and III in mV)
Occurrence of non-sustained ventricular tachycardia (Holter monitoring, exercise testing)
Heart failure signs and/or symptoms or arrhythmias necessitating medical treatment according to the guidelines and likely due to arrhythmogenic cardiomyopathy
*Secondary endpoints*
All individual components of the primary endpoint
Diagnosis of DCM (according to Mestroni criteria [19])
Diagnosis of ARVC (according to revised task force criteria [18])
Development of global or regional dysfunction and structural alterations (according to revised task force criterion 1 [18])
QRS axis (12-lead ECG)
Conduction intervals (PR interval, QRS duration [12-lead ECG; SA-ECG])
STT segment changes (12-lead ECG)
Change in biomarkers
Occurrence of sustained ventricular tachycardia or ventricular fibrillation
Hospitalisation for a cardiovascular reason

*LV* left ventricular, *CMR* cardiac magnetic resonance*, RV* right ventricular,* ECG* electrocardiogram,* DCM* dilated cardiomyopathy, *ARVC* arrhythmogenic right ventricular cardiomyopathy,* SA-ECG* signal-averaged electrocardiography

^a^The primary endpoint is a multiparametric assessment of disease progression defined as a responder-based composite primary endpoint. If one of the predefined parameters of the composite primary endpoint is reached, CMR imaging is performed and study end date recorded

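### The Abstract and Discussion place cardiovascular death in the primary endpoint, but Table 3 lists no death, so a sudden death could be censored or carried forward as no change

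*Protocol article*

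**What the plan says.** The protocol article describes the primary endpoint in three places.

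- **Abstract, Methods:** the composite covers CMR and ECG parameters and also "signs and/or symptoms related to DCM and ACM, and cardiovascular death".
- **Discussion:** the same list is repeated, ending with "signs and/or symptoms related to DCM and ACM, and cardiovascular death is adopted as the primary endpoint".
- **Study endpoints:** "The primary endpoint is a multiparametric assessment of disease progression defined as a responder-based composite primary endpoint (Tab. 3". Table 3 then gives eight primary components. Five are CMR changes, one is a fall in QRS voltage, one is "Occurrence of non-sustained ventricular tachycardia (Holter monitoring, exercise testing", and one is "Heart failure signs and/or symptoms or arrhythmias necessitating medical treatment according to the guidelines and likely due to arrhythmogenic cardiomyopathy".

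Death from any cause appears nowhere in Table 3. The secondary list does contain "Occurrence of sustained ventricular tachycardia or ventricular fibrillation", cardiovascular hospitalisation, and each component of the primary endpoint.

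On analysis, the Statistical analysis section says: "The primary outcome will be presented by Kaplan-Meier curves for the treatment group, followed by the stratified log-rank test using stratification variables". It adds: "For missing data, the last observations made will be used". It gives no rule for a participant who dies. The Baseline results section reports that, after recruitment stopped early, the components are to be analysed as continuous measures in place of the dichotomous composite.

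**The concern.** The document gives two different primary endpoints, one with cardiovascular death and one without. The difference matters in this disease: the Introduction counts sudden cardiac arrest as part of the phenotype and names prevention of sudden cardiac death as a possible benefit of early treatment.

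If Table 3 is applied as printed, the worst outcome of the disease might not count as progression. The last-observation rule might even record it as a stable heart. The resulting bias could run either way. It would dilute a benefit if such deaths fell mainly among controls, and flatter eplerenone if they fell mainly in the treated arm.

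**Working it through.** **1. The plan's own figure.** The sample size assumes 50% against 25% at 3 years, alpha 0.05 and at least 80% power. A two-sided Fisher exact test, fully enumerated, has power 79.4% at 63 per arm and 80.2% at 64 per arm, so 2 × 64 = 128 is reproduced. Allowing for loss to follow-up gives 128 / 0.90 = 142.2, so 143, and 128 / 0.85 = 150.6, so 151. Both are consistent with the target of 150. The 50% is assumed for the composite as a whole, so this calculation does not depend on whether death is in the list. The rest of the check is textual.

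**2. Does any Table 3 component capture a sudden death?** Take a carrier who dies suddenly and untreated, with no component reached before.

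- Five CMR components: each needs a follow-up scan, and there is none.
- QRS voltage: needs a follow-up ECG that crosses the threshold, and by assumption none did.
- Non-sustained ventricular tachycardia: counted on Holter or exercise testing only.
- Heart failure or arrhythmia: requires that medical treatment be needed. A treated arrhythmia would qualify. An unwitnessed death with no arrhythmia recorded or treated does not clearly qualify.
- Sustained ventricular tachycardia or fibrillation: secondary only, and it has to be documented.

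No component is plainly met. The instruction to perform CMR once a component is reached also presupposes a living participant.

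**3. Time-to-event reading.** If the death is not an event, the natural handling in a Kaplan-Meier and log-rank analysis is censoring at the date of death. That treats the carrier as having the same later risk of progression as carriers who remain under observation, which is not credible for a cardiovascular death.

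**4. Last-observation reading.** The Treatment section and Table 2 schedule CMR at baseline and 36 months only, plus a scan when a component is reached. For this carrier the last CMR value is the baseline value, so

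change = last value − baseline value = baseline − baseline = 0

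for five of the eight components. ECG and Holter are yearly, so their last value is the latest annual visit before death, which by assumption had not crossed a threshold.

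**5. After the amendment.** On a continuous scale a death has no value of its own. If death is treated as missing data, step 4 applies directly and the five CMR changes enter the comparison as exact zeros.

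**The case against.** The strongest reply has four parts.

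- **Table 3 governs.** The methods text points only to Table 3, while the other wording sits in an abstract and a discussion. What the adjudication committee actually works from is not shown. This stands to the extent that a reader might infer the committee holds two incompatible definitions, and the documents do not establish that. It does not remove the contradiction. The shorter summaries contain a component that the detailed table lacks, which is the reverse of condensing.
- **Handling of death belongs in the analysis plan.** That plan was amended and is not shown. A reader might infer that deaths will be censored or carried forward. The article says neither, and does not say that death counts as missing data. Both are possible consequences of its wording, not stated rules.
- **The size is unknown.** A reader might be tempted to express one misclassified death as a share of the expected composite events, or as a loss of power. Such figures rest on the dichotomous composite, which no longer applies to the 84 participants, and on a number of deaths that the documents do not give. Entry criteria (NYHA class I, preserved ejection fraction, no non-sustained or earlier sustained arrhythmia) also make deaths unlikely.
- **Other wording differences are minor.** The Abstract and Discussion speak of ventricular ectopy where Table 3 has non-sustained ventricular tachycardia. That is a summary label for a listed item, and no passage sets a count of premature beats as an endpoint. The summaries also name DCM and ACM where Table 3 names arrhythmogenic cardiomyopathy alone. A strict reader could see ambiguity for a DCM-type heart failure event, but the Discussion stresses the overlap of the two conditions. This merits at most a clarification.

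**Conclusion.** The point holds as an internal contradiction in the definition of the primary endpoint. Two places include cardiovascular death; the table that defines the endpoint lists it neither as primary nor as secondary. Read literally, a sudden death without an earlier treated arrhythmia or other component is no event. It could be censored, or could enter as zero change on five of the eight components.

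This rests on two assumptions: that Table 3 is applied as printed, and that a death is treated as censored or missing because nothing in the article directs otherwise. The number of participants affected is unknown and probably small, so no percentage is attached. The point is still worth settling, because the affected outcome is the most severe one and the correction is cheap. The amendment does not resolve it; it moves the risk mainly to carried-forward continuous values.

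**What to change.** 1. Reconcile the Abstract, Table 3 and the Discussion, so that Table 3 lists cardiovascular death as a progression event, as the other two already state. It then also becomes a secondary endpoint, since Table 3 makes every primary component one.
2. State before database lock that no value is carried forward after cardiovascular death in the continuous-component analyses, and pre-specify the handling. A worst-rank analysis or a composite-strategy sensitivity analysis would serve; other approaches are defensible if fixed in advance.
3. As a minor clarification, use the same DCM and ACM wording in Table 3 as in the summaries.

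The cost is a few lines in Table 3, the analysis plan and any adjudication charter, plus one small sensitivity analysis. No new data are needed beyond the date and adjudicated cause of any death.
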